#### Hypothesis 3 (H3)

Those in both the IO and IMI conditions will experience a reduction in gambling expenditures over the course of treatment. However, this reduction is expected to be more pronounced for those in the IMI condition.

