#### Hypothesis 4 (H4)

Reductions in gambling frequency and severity for both the IO and IMI conditions will be positively correlated with time spent using the online self-help tools (i.e., more time spent online will be associated with greater reductions in gambling frequency and severity).

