#### Hypothesis 5 (H5)

The IMI group will demonstrate greater adherence (i.e., more modules completed on the self-help website) compared to the IO group.

In addition to the four hypotheses listed above, one exploratory research question will be examined to determine the impact of each treatment condition on participants’ attitudes toward treatment. Attitudes are important to probe considering common pre-existing reluctance to engage in professional treatment in this population. The following research question will be examined:

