### Data analyses

All statistical analyses will be conducted using SPSS version 26.0 at 12- and 24-month follow-up time points. Following completion of the 24-month follow-ups, the trial will be terminated. If baseline data are missing completely at random, they will be handled using the full imputation maximum likelihood approach to estimate means, variances, and covariances. Missing data at follow-ups will be handled with the multiple imputation method. Analyses will be conducted using the intention-to-treat (ITT) approach. Bivariate comparisons of all demographics and outcome measures will be conducted to explore differences between groups at baseline. Chi-square tests of independence will be used to compare groups on categorical measures, while *t* tests will be used to compare groups on continuous measures. Any primary outcome variables with significant differences between groups will be controlled for by entering them in as covariates in primary and secondary analyses. It is likely that the primary outcome variables will appear non-normally distributed when assessed with q-q plots and Shapiro-Wilk tests; in these cases, data will be appropriately transformed to achieve normality. If the data transformations are unsuccessful, separate nonparametric analyses will be conducted as appropriate instead of the respective planned analyses outlined below. Additionally, chi-square tests of independence will be used to determine if attrition rates differ in terms of treatment group or baseline characteristics.

H1 and H2 will be analyzed using generalized equation estimation (GEE) to determine if there are group (IO; IMI) differences in change over time. Outcome variables will include gambling frequency (i.e., number of days gambled in the last month), expenditures (i.e., average number of dollars lost per gambling day), and severity (i.e., NODS score). GEE is advantageous because it can account for the natural correlations over time in longitudinal data [38].

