To aid in clinical significance and translation, H1 and H2 will also be analyzed categorically with two separate logistic regressions. Both analyses will include Group and Time as binary predictors. The analysis to test H1 will include gambling disorder status (meets criteria; does not meet criteria) as the binary outcome. The analysis to test H2 will include recovery status (abstinence; improvement; no improvement) as the multinomial outcome. Improvement is defined as at least a 50% reduction in average number of dollars lost per gambling session.

H3 will be analyzed with a bivariate Pearson correlation between time spent on the site and change in dollars spent per gambling day from baseline to follow-ups.

H4 will be analyzed with two bivariate comparisons. Two unpaired *t* tests will be conducted to determine if the adherence rates differ by group after the 12- and 24-month follow-ups. Adherence will be measured in two ways: (1) number of modules completed on the program and (2) total time spent on the program website.

To test the exploratory research question, bivariate comparisons will be conducted. Q1 will be analyzed with an unpaired *t* test comparing group treatment ratings at each of the follow-up periods (3, 6, 12, and 24 months).

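### The hypothesis labels in the analysis section do not match H1–H5, and H4 as stated has no planned test

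*Protocol article*

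**What the plan says.** The Objectives section of the protocol article sets out five hypotheses. H1 concerns gambling frequency, H2 problem severity and H3 expenditures, each with a larger reduction expected in the IMI arm. For H3 the opening statement is "Those in both the IO and IMI conditions will experience a reduction in gambling expenditures over the course of treatment". H4 concerns use of the website: "Reductions in gambling frequency and severity for both the IO and IMI conditions will be positively correlated with time spent using the online self-help tools". H5 concerns adherence: "The IMI group will demonstrate greater adherence (i.e., more modules completed on the self-help website) compared to the IO group". The text directly after H5 counts the hypotheses as four.

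The Sample size estimation section bases the calculation on H1–H3, then speaks of two superiority hypotheses on three primary outcome measures, and promises Bonferroni corrections.

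The Data analyses section assigns:
- a GEE analysis of frequency, expenditures and NODS score to H1 and H2;
- a logistic regression on gambling-disorder status to H1;
- a logistic regression on recovery status, with improvement defined by dollars lost, to H2;
- a usage correlation to H3: "H3 will be analyzed with a bivariate Pearson correlation between time spent on the site and change in dollars spent per gambling day", taken from baseline to the follow-ups;
- between-arm t tests of modules completed and total site time to H4: "H4 will be analyzed with two bivariate comparisons".

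No analysis carries the label H5.

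**The concern.** A pre-specified plan should let a reader trace each hypothesis to the test that supports it. Here the label H3 leads from a comparison between randomised arms to a correlation that contains no arm comparison. The label H4 leads from a usage–outcome association to an arm comparison of adherence. The two categorical analyses carry the labels of constructs that they do not measure.

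Two things are at stake. If H4 is left as it is, the outcome correlated with site time could be chosen from dollars, days or NODS score after the data are seen. If the number of primary hypotheses stays unclear, so does the Bonferroni divisor, and a p value between the two candidate thresholds could be called either way.

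**Working it through.** The labels involve no arithmetic, so each hypothesis is set beside the analysis that bears its number and the analysis that matches its content.

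| Hypothesis | Content as stated | Analysis under that number | Analysis that matches the content |
|---|---|---|---|
| H1 | Frequency, by arm | GEE; also gambling-disorder status | GEE on days gambled |
| H2 | Severity, by arm | GEE; also recovery status | GEE on NODS score; gambling-disorder status |
| H3 | Expenditures, by arm | Site time vs change in dollars | GEE on dollars lost per gambling day; recovery status |
| H4 | Site time vs reductions in frequency and severity | t tests of adherence by arm | None |
| H5 | Modules completed, by arm | None | t tests labelled H4 (first adherence measure) |

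The Strengths and limitations section confirms the categorical rows. It describes the first classification as one of NODS scores and the second as one of changes in expenditures.

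**Does a simple renumbering repair the section?** Move every analysis label up by one.
- Gambling-disorder status becomes H2, which fits.
- Recovery status becomes H3, which fits.
- The t tests become H5, which fits.
- The GEE becomes H2 and H3, which drops H1 although frequency is one of its outcomes.
- The site-time correlation becomes H4, which is the right kind of analysis with the wrong outcome: dollars, where H4 names frequency and severity.

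A list of four hypotheses, with frequency and severity joined as the first, would explain the labels, the count of four and the count of two superiority hypotheses on three outcomes. That is only an inference. Even on that reading, H4 and its correlation name different outcomes.

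**Bonferroni divisor.** The overall alpha is .05 (Sample size estimation). The same paragraph gives two counts for the primary analysis:
- two superiority hypotheses: .05/2 = .025;
- three outcomes, or H1–H3: .05/3 = .0167.

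A primary p value between .0167 and .025 would pass under the first and fail under the second.

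**Correlations needed for H4.** There are two outcomes (frequency and NODS score).
- Pooled over arms: 2 per follow-up time, or 2 × 2 = 4 over the 12- and 24-month analyses.
- By arm: 2 × 2 = 4 per follow-up time, or 4 × 2 = 8 over both.

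**The case against.** The best defence is that nearly all of this is numbering that a careful reader can resolve, and much of it stands. Three stronger readings are tempting, and the documents do not support them.

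- A reader might infer that the randomised comparison of expenditures has been replaced by a correlation. It has not. The Data analyses section names dollars lost per gambling day as a GEE outcome for group differences in change over time, and the Objectives section lists expenditures as a primary outcome.
- A reader might infer that H5 is not analysed. The t tests labelled H4 compare modules completed by arm, which is H5's own definition of adherence.
- A reader might carry the Bonferroni range down to .05/4 = .0125 or .05/5 = .010. The correction is promised in the paragraph on the primary outcomes, and nothing ties it to the usage or adherence hypotheses. Only two versus three is open.

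It can also be said that H4 is a non-randomised association outside the primary outcomes. That is true and limits the weight of the gap, but it does not close it: no planned analysis relates site time to change in frequency or NODS score. Nor is this detail left to a fuller document, because the article itself names an outcome for the correlation, and it is not the one in H4.

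**Conclusion.** The point holds in a limited form. All five label assignments in the analysis section need amending. Four of them (the GEE, the two categorical analyses and the adherence t tests) are label faults, because their content serves H1, H2, H3 and H5. The fifth, the site-time correlation, is a fault of substance: H4, one hypothesis of five, has no test as stated under any numbering. The conflicting counts leave the primary Bonferroni threshold unclear between .025 and .0167.

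The randomised primary comparisons are planned, and this point does not invalidate them. The conclusion rests on the article as published. It takes the hypothesis list as the statement of intent and the GEE sentence as covering all three outcomes that it names. H4's reference to both conditions is not read as requiring separate correlations within each arm; a pooled analysis is also a fair reading.

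**What to change.** 1. Relabel the GEE as H1 (frequency), H2 (NODS score) and H3 (expenditures).
2. Relabel gambling-disorder status as the categorical analysis of H2 and recovery status as that of H3.
3. Relabel the adherence t tests as H5, with modules completed as the defining measure and total site time as supportive.
4. For H4, add correlations of site time with change in days gambled and change in NODS score, state whether they are pooled or by arm, and keep the dollars correlation as exploratory. Alternatively, restate H4 before analysis so that it names the planned outcome.
5. Correct the count of four hypotheses in the text after H5 and the count of two in the Sample size estimation section. State that the primary Bonferroni family is the three outcomes of H1–H3, so the threshold is .0167. This is a design choice, and it agrees with the stated basis of the sample size.

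The cost is wording plus two correlations per follow-up time if pooled, or four if by arm. They use the frequency and NODS variables already named for the GEE and the site-time data already planned, so no new data are needed.

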**Table 1 Tab1:**
[figure not shown]
Schedule of enrolment, interventions, and assessments

Participants will be invited via email to complete follow-up assessments at 3, 6, 12, and 24months after their enrolment in the study. They will not be dropped from the study unless they explicitly request to withdraw by contacting the research team as indicated in the consent form. Participants who drop out or require ancillary or post-trial care will be provided with local resources (e.g., contact information for crisis lines, emergency departments, family physicians, etc.) and encouraged to create a non-research account with the online program.

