### Intervention conditions

#### Internet only (IO)

This treatment group will be provided with access to an online workbook (www.gamblingselfhelp.com) based on a paper version mentioned earlier [10] that has demonstrated efficacy in multiple trials [11–14]. It consists of cognitive-behavioral self-help tools to reduce problem gambling. These tools are organized into four modules: self-assessment, goal setting, goal implementation, and goal maintenance. The design of the modules allows for the provision of concise cognitive-behavioral strategies for controlling or abstaining from gambling. The activities within each module may be completed in any order and as many times as desired. None of the activities is mandatory. Participants will have unrestricted access to the site for the entire duration of the study in order to mimic other web resources as much as possible in terms of accessibility.

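### The correlation of site time with improvement (H4) sets no order between use and outcome and makes no allowance for arm, so neither a null, a negative nor a positive result can be read clearly

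*Protocol article*

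**What the plan says.** Hypothesis 4 states that reductions in gambling frequency and severity, in both conditions, will be "positively correlated with time spent using the online self-help tools", and explains that "more time spent online will be associated with greater reductions in gambling frequency and severity".

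The matching analysis, in the Data analyses section, is a "bivariate Pearson correlation between time spent on the site and change in dollars spent per gambling day from baseline to follow-ups". That section labels it H3 and uses an expenditure outcome in place of H4's frequency and severity. By content it can only be the H4 test. The label and the outcome are a separate inconsistency that must be reconciled.

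On exposure, the Internet only (IO) section says "Participants will have unrestricted access to the site for the entire duration of the study" and "The activities within each module may be completed in any order and as many times as desired". The IMI arm has the same access. Participants are invited to "follow-up assessments at 3, 6, 12, and 24months after their enrolment in the study", and "All statistical analyses will be conducted using SPSS version 26.0 at 12- and 24-month follow-up time points".

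The adherence comparison between arms (H5 by content, labelled H4 in Data analyses) uses two measures: "1) number of modules completed on the program and (2) total time spent on the program website".

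**The concern.** The programme has no end point. A participant who recovers early can stop using it, and one who is still gambling, or relapses, has a reason to come back. The Introduction says the parent workbook covers planning for relapse, and the site has a goal-maintenance module. Time on the site may therefore be partly a response to lack of improvement.

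The outcome windows add to this. The expenditure questions and the NODS look back three months (Baseline and follow-up assessments). Site time counted up to a 12- or 24-month visit thus includes use during the very months being scored.

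Arm acts in the other direction. H1 to H3 expect the interview to increase improvement, and H5 expects it to increase use. If both hold, a correlation across the pooled sample is partly produced by arm.

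At stake is Hypothesis 4. A workbook whose early use helps could show no association or a negative one, and a positive one could come partly from arm or from motivation.

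**Working it through.** **No figure to reproduce.** The protocol gives no effect size, power or sample size for this correlation. For context, 108 per group is 216 in all, and 216 / (1 - 0.20) = 270, the planned total. With 216 participants, two-sided alpha 0.05 and 80% power, the smallest detectable correlation is about 0.19.

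**Return use.** All inputs here are assumptions. Let early use E have SD 1 and let the reduction R have SD 1, with corr(E, R) = b = 0.30. Let later use be L = k(-gR + noise with SD s), where g is the strength of return use by people who improve less and k is the scale of later use. Total time is E + L. Then

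- cov(E + L, R) = b - kg
- var(E + L) = 1 + k²(g² + s²) - 2kbg
- r(total, R) = (b - kg) / sqrt[1 + k²(g² + s²) - 2kbg]

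| Assumed later use | g = 0 | g = 0.3 | g = 0.6 |
|---|---|---|---|
| k = 1, s = 1 | 0.30/√2.00 = 0.21 | 0/√1.91 = 0.00 | -0.30/√2.00 = -0.21 |
| k = 1, s = 0.5 | 0.30/√1.25 = 0.27 | 0/√1.16 = 0.00 | -0.30/√1.25 = -0.27 |
| k = 0.25, s = 1 | 0.30/√1.0625 = 0.29 | 0.225/√1.023 = 0.22 | 0.15/√0.995 = 0.15 |

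Early use alone gives 0.30 in every cell. The sign turns only when kg exceeds b. With k = 1 that means g above 0.30. With k = 0.25 it means g above 0.30 / 0.25 = 1.2.

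Simulation of the second row's model with 216 participants (4,000 runs per setting) shows what this does to a test at 0.05:

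- g = 0: significant positive correlation in 98% of runs
- g = 0.25: mean r 0.05, significant positive in 10%
- g = 0.50: mean r -0.18, significant positive in 0% and significant negative in 77%

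**Pooling of arms.** Suppose use and improvement are unrelated within each arm, the arms are equal in size, and they differ by d1 SD in use and d2 SD in improvement. The pooled correlation is (d1·d2/4) / sqrt[(1 + d1²/4)(1 + d2²/4)]. Take d2 = 0.20, the effect named in Sample size estimation, and assume d1.

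- d1 = 0.20: 0.01 / 1.01 = 0.01
- d1 = 1: 0.05 / √(1.25 × 1.01) = 0.04

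At the design effect, arm alone contributes little. Its share grows with larger arm differences.

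**Timing of a cut at 3 months.** Use from enrolment to month 3 ends before the 6-month outcome's look-back (months 3 to 6) begins.

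**The case against.** The strongest reply is that H4 claims only an association, and a Pearson correlation tests an association. No such correlation can show direction, and the randomized comparisons under H1 to H3 do not depend on it. That stands, and it limits the point to how H4 is tested and read. But H4 is directional, and readers will take it as evidence on the benefit of use.

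A second reply is that an article may leave the exposure window to a fuller document. This stands in part, since whether site time is cut at each follow-up is unstated. A cut at the visit would still count use prompted by poor progress before it. The article has also fixed the statistic as bivariate, which excludes arm and baseline value. H4's mention of both conditions could mean one correlation per arm, but the analysis sentence does not say so.

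Three stronger readings are tempting and unsupported:

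- A reader might infer that 24-month totals will be set against 3- or 6-month change, so that use after the outcome is counted. The word total occurs only in the adherence sentence, and analyses are placed at 12 and 24 months.
- A reader might infer that the correlation will be reversed. With small later use (k = 0.25) it falls only to 0.22 or 0.15. Motivated people may also both use the site more and improve more, which biases it upwards.
- A reader might infer that comparing cumulative use between arms is invalid. It is a randomized comparison and valid as a comparison of use. That lower use may reflect earlier recovery is a matter of interpretation.

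**Conclusion.** The point holds in limited form. As written, the H4 test relates site time of unstated window to change from baseline. It does not ensure that use precedes the scored period, and it does not adjust for arm or baseline value. Return use by people still gambling can weaken the correlation and, if strong enough, reverse it. Pooling of arms, or motivation, can inflate it.

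Neither the size nor the net direction can be derived from the documents. The range of 0.29 to -0.27 around a true early-use correlation of 0.30 rests wholly on assumed values of g, k and s. The part due to pooling is about 0.01 to 0.04 under the assumptions shown. The change should be made because it is cheap and improves what H4 can say. It does not bear on the primary randomized comparisons.

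**What to change.** 1. Reconcile the label and the outcome of the use-improvement analysis with Hypothesis 4.
2. Main H4 analysis: relate site time and modules logged from enrolment to the 3-month follow-up to each outcome at 6, 12 and 24 months, by regression or partial correlation adjusted for arm and baseline value.
3. Sensitivity analysis: adjust also for the 3-month outcome. Use in months 0 to 3 can itself respond to early change, and change from baseline includes change in those months, so the cut alone does not settle the order.
4. Keep cumulative site time as a secondary, descriptive association, and state the window used.
5. Report the result as an association, not as an effect of use.
6. Keep the randomized between-arm comparison of cumulative modules and time, add one for months 0 to 3, and note that lower later use may reflect earlier recovery.

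Cost: analysis wording, and cutting the user data at 3 months. The User data section lists time, module status and number of log-ons but does not say that records are dated, so this must be confirmed first. Use after 3 months, and the 3-month outcome as an endpoint, drop out of the main H4 test.

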### Sample size estimation

The sample size was determined based on previous work exploring self-directed gambling interventions [11–14] and was computed using G*Power [36] on the basis of H1–H3. The estimation method was based on a repeated-measures between-factors ANOVA, which serves as a simpler derivative of the general linear model that the primary analyses will be based on [37, 38]. Two superiority hypotheses using three primary outcome measures will be analyzed using conventional two-tailed tests with thresholds of power = .80 and *α* = .05. Bonferroni corrections will be calculated to account for multiple comparisons. Correlations of *r* = .50 between baseline and follow-up data were accounted for [16]. A sample size of 108 participants per group will permit statistical detection of small effect sizes (Cohen’s *d* = 0.20 for continuous measures) at the specified significance level. This translates to differential detection of approximately 2 days less gambling per month and a 1-point decrease in NODS scores [37]. After accounting for 20% attrition over 12 months, the resulting planned sample size is 270 participants.

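### The correlation meant to test whether site use goes with improvement has no arm term, although the plan expects the arms to differ on both variables; the distortion is small but free to remove

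*Protocol article*

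**What the plan says.** H4 states that "Reductions in gambling frequency and severity for both the IO and IMI conditions will be positively correlated with time spent using the online self-help tools". The hypothesis thus names both conditions and is worded as an association.

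The only test in the Data analyses section that relates site time to change is a "bivariate Pearson correlation between time spent on the site and change in dollars spent per gambling day from baseline to follow-ups". The section attaches it to H3, but H3 in the list of hypotheses is the between-arm expenditure hypothesis. The content matches H4, except that the test uses dollars, whereas H4 says that "more time spent online will be associated with greater reductions in gambling frequency and severity".

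The test is described as bivariate, with no arm term and no baseline covariate. The text does not say whether the arms are pooled or analysed separately. The section's covariate rule applies only when a primary outcome differs significantly between arms at baseline, so it does not bring arm into this analysis.

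Two other hypotheses bear on this. H3 expects a larger fall in spending in the interview arm, and H5 says that "The IMI group will demonstrate greater adherence". The Data analyses section counts total time on the website as one of its two measures of adherence, so the variable being correlated is itself expected to differ by arm.

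**The concern.** H4 asks whether, in each condition, people who use the site more improve more. A correlation over all participants mixes that within-arm relation with a between-arm one. If the interview raises site time and separately lowers spending, the interview arm lies higher on both axes and the pooled correlation is positive, even if use and change are unrelated inside either arm. A significant coefficient could then be read as support for H4 when it partly repeats H3 and H5.

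A second question is baseline level. Change from baseline is arithmetically tied to the baseline value, and how much each person uses the site is that person's own choice. A relation between site time and baseline spending could therefore affect the result, in a direction that depends on how it arises.

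**Working it through.** **Inputs from the protocol.** Sample size estimation gives 108 per arm (216 in total), d = 0.20, "conventional two-tailed tests with thresholds of power = .80 and *α* = .05", and "Correlations of *r* = .50 between baseline and follow-up data were accounted for". Allocation is 1:1. The protocol gives no power or effect size for this correlation. Its overall figure reproduces: 216 / (1 − 0.20) = 270. The same section says "Bonferroni corrections will be calculated to account for multiple comparisons" without the number of tests, so nominal 5% is used below.

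**Assumed inputs (not in the protocol).** The arm difference in site time, dx, is taken as 0.2 to 0.8 SD. The correlation of site time with baseline spending, q, is taken as 0 to .3.

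**1. Arm difference alone, arms pooled.** With r = .50 and equal variances, the SD of change is √(2(1 − .5)) = 1 outcome SD, so d = 0.20 carries over to change as dy = 0.20. With no relation inside either arm, the pooled correlation is

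r = (dx·dy/4) / √((1 + dx²/4)(1 + dy²/4)).

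For dx = 0.3 and dy = 0.2: r = 0.015 / √(1.0225 × 1.01) = 0.0148. By Fisher's z, the shift is 0.0148 × √213 = 0.22, and the two-sided rejection rate is 5.5%.

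| dx (use) | dy (change) | pooled r | rejection, n = 216 |
|---|---|---|---|
| 0.2 | 0.2 | 0.010 | 5.2% |
| 0.3 | 0.2 | 0.015 | 5.5% |
| 0.5 | 0.2 | 0.024 | 6.4% |
| 0.8 | 0.2 | 0.037 | 8.4% |
| 0.5 | 0.5 | 0.059 | 13.8% |

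Simulation (6,000 runs) gave 5.3% for the second row, 6.0% for the third and 13.3% for the last.

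**2. Baseline level, under two data models that both have r = .50.** Site use has no effect on outcome in either model, and there are no arm effects.

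*Model A: use depends on the observed baseline value.* The reduction correlates (1 − .5)/1 = .50 with baseline, so use correlates q/2 with the reduction. For q = .1, .2 and .3, the planned correlation rejects 11%, 31% and 60% of the time. Regressing follow-up on use, baseline and arm rejects about 5%.

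*Model B: use depends on a stable gambling level, and baseline and follow-up are two noisy readings of it.* Use then has covariance q with both readings, so its correlation with the reduction is 0 and the planned test holds about 5%. The partial correlation of use with follow-up, given baseline, is

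(q − .5q) / √((1 − q²)(1 − .25)) = .577q / √(1 − q²).

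For q = .2 this is .118. With √(216 − 2 − 3) = 14.5, the shift is 1.72 and rejection about 40%. For q = .1 and .3 it is about 13% and 76%. Nearly all of these rejections make site use look harmful.

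At q = 0 neither model inflates either analysis.

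**The case against.** A reader might infer something stronger: that regression to the mean invalidates the planned test, and that adjusting for baseline corrects it. Model A's 31% and 60% invite that reading. The documents do not support it. They give r = .50 but not the mechanism behind it, and they give no correlation between site time and baseline spending. The expenditure measure is a three-month retrospective self-report, so Model B is at least as plausible. Under Model B the change-score test is sound and the baseline-adjusted one fails. Baseline adjustment for a non-randomised exposure is a choice between biases.

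A reader might also infer that the arm difference alone seriously inflates the test. At the plan's own d it does not.

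Three further defences have force:
- The article never says that the arms are pooled. H4's wording, "for both the IO and IMI conditions will be positively correlated with time spent using the online self-help tools", is compatible with separate correlations, and follow-ups are in the plural. Against that, the sentence on the test names no group, whereas neighbouring analyses do where group matters.
- H4 is an association, and a marginal correlation does test its literal wording. The risk lies in how a significant result is read.
- The sample size rests on H1–H3 and site use is a secondary outcome, so no randomised comparison is affected.

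What survives is that nothing in the stated test separates the arms, although the hypothesis names both.

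**Conclusion.** The point holds in a limited form. The use–change correlation is specified without arm, while the plan predicts that arm moves both variables. If the arms are pooled, rejection at a nominal 5% rises to about 5% to 8% at d = 0.20, and to about 13% if both arm differences are 0.5 SD. These figures assume n = 216, no relation within either arm, and an arm difference in use that the protocol does not state. If the correlation is run separately by arm, this inflation disappears.

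Baseline level is a matter for sensitivity analysis. Its effect rests on an assumed q and an unknown mechanism, and neither the change-score analysis nor the baseline-adjusted one can be called correct on what the protocol gives.

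**What to change.** 1. Estimate the use–change relation with arm in the model, by a partial correlation given arm or a regression with an arm term. Show the slope within each arm or add a use-by-arm term, because H4 speaks of both conditions. Within-arm estimates will be less precise: the standard error of Fisher's z is 1/√105 = 0.098 for one arm of 108, against 1/√213 = 0.069 for all 216.
2. Report the result with and without adjustment for the baseline value, as a sensitivity check. State that the change-score version is biased if use depends on the observed baseline, and that the adjusted version is biased if use depends on a stable level measured with error.
3. Say in advance that a significant result will be reported as an association, since site time is not randomised.
4. Correct the label from H3 to H4, and reconcile the outcome (dollars per gambling day) with the frequency and severity that H4 names.

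The arm term and its interaction cost one or two degrees of freedom. All variables are already collected, and neither the sample size nor the primary analyses change.
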